### Study interventions

**The modelling-based narrative intervention** will adopt an eclectic approach that integrate behavioural modelling and a narrative approach to promote knowledge and skill internalisation and retention (Table 1). The intervention will offer a vivid decision making experience to the participants. Participants of the intervention group will receive a modelling-based narrative intervention to be delivered by RA1. He/she will receive 3-days of intensive training from the investigation team on AMI management and care-seeking, principles and skills of group facilitation and counselling, and the ways of delivering the study protocol, accordingly.

The 7-week intervention consists of three weekly 90-minute face-to-face sessions in a small group of 6-8 participants, followed by a half-day booster session one month after the three weekly sessions (Figure 2). The small group format is adopted because it is effective in providing peer support and facilitating peer learning. Each of the face-to-face sessions will begin with a brief educational presentation on a relevant topic by the intervener. These weekly topics are coherent with the critical junctures that people commonly encounter when they make care-seeking decisions in the context of AMI. They include: (1) symptom recognition and risk identification, (2) emotional response to possible AMI attack and perceived barriers and facilitators to care-seeking, and (3) means of care-seeking and transportation. To optimise the effects of teaching and learning, coloured pictures and interactive skills will be used to illustrate the health information. Emphasis will be placed on enhancing patients' understanding of the symptom manifestations, disease pathophysiology, nature of disease progression, principle of treatments, appropriate care-seeking behaviours and realising the significance of their prompt care-seeking behaviours in making a difference to their health outcomes. The education content of each session complies with the latest international practice guidelines and recommendations published by the European Society of Cardiology and American Heart Association. The content has been validated by a panel of experts, including cardiologists, advanced practice nurses and nursing academicians in cardiac care.

After the structured educational sessions, the participants will then be offered a virtual AMI attack experience through an interactive video presentation, to consolidate their knowledge gained in previous structured educational sessions through a vivid experience. Video-based intervention is

selected as a meta-analysis reported that audio and video-based narrative interventions were more effective in changing the attitudes, intentions and behaviours when compared to paper-based narratives. To engage the participants in an active learning process, a narrative storytelling approach will be adopted in each face-to-face session. A video captures a model patient in enacting the scenes of going through the perceptual-cognitive processes, including the symptom experience, symptom interpretation and the care-seeking process, to offer a mental rehearsal for the participants. The video will be paused at the four critical junctures to allow participants to outline their own decision-making process. Each pause will occur at each weekly session, with the focus on one critical moment as mentioned above. During the pause, the intervener will encourage the participants to discuss their feelings, concerns and difficulties in making their care-seeking decisions. The intervener will act as the facilitator to assist participants to solicit the application of their knowledge gained from previous educational presentation sessions, and facilitate them in making appropriate judgements and decisions. He/she has to use non-judgmental, accepting, empathetic and respectful attitudes to encourage the participants to disclose their real concerns. The intervener will also guide the participants to brainstorm resolving methods for each of the barriers that have been identified during the session. He/she will also clarify all the misbeliefs related to AMI and care-seeking. Interactive teaching strategies, such as role-play and scenario-based group activities will be adopted to facilitate the learning process. Emphasis will be placed on assisting participants in grasping the skills of symptom recognition, handling the emotional responses upon symptom onset, overcoming perceived barriers and mastering the decision-making process.

At the end of each face-to-face session, a video sharing the personal experiences of real patients will be used to enhance participants' self-efficacy through peer-modelling. In particular, the sharing will include patients with varied, but similar, backgrounds as the participants, including patients with experience of coping with the critical junctures successfully and demonstrating good recovery from the disease. Patients will also be included who delayed action when experiencing AMI symptoms and thus jeopardised their health, sustaining post-AMI complications. Such peer modelling can secure participants' understanding of how their actions can make a difference to their health outcomes. The storytellers will share their real-life stories, with the emphasis placed on helping the participants to identify strategies to overcome the difficulties in decision-making.

A half-day booster session will be delivered one month after the completion of the face-to-face sessions. This booster session serves to reinforce the knowledge and decision-making skills gained from the face-to-face sessions. A scenario-based approach will be adopted to optimise participants' perceptual-cognitive processes in labelling and interpreting AMI symptoms. Five scenarios with various perceptual, social and contextual circumstances have been developed to offer a cognitive rehearsal for the participants to handle different situations (Table 2). The intervener will facilitate the participants going through the perceptual-cognitive processes for each scenario. Participants will be encouraged to express perceived barriers that exist during the decision-making course and their concerns. The intervener will encourage them to recall and apply the knowledge and skills that were

acquired in previous face-to-face sessions to resolve every situational dilemma.

**A didactic education on AMI care-seeking** will serve as the **control intervention**. It consists of one session to be delivered in a small group (6–8 participants/group) format by another RA (RA2). The factual information about AMI and the appropriate response towards possible symptoms will be delivered with a structured PowerPoint slide-set. Narrative approach and booster sessions will not be used in the control group. The intervener will answer questions from the participants when asked, according to the structured education content for the control group. The questions and topics discussed will be recorded for subsequent data interpretation. During the conversation, the RA will not use any wordings which is related to patient's privacy (e.g. patient's name, address etc.) and will only use a subject code to label all the audio records. Permission of audio recording of the conversation will be obtained in the informed consent and before the start of the conversation as well.

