### Study design

This is a sequential mixed-method study consisting of a randomised double-blind controlled trial and an exploratory qualitative study. The study implementation protocol is outlined in Figure 1. A research assistant (RA1) will recruit eligible participants from the cardiac clinics and wards of four regional hospitals in Hong Kong. The study sites are leading hospitals providing cardiac care services within the region. He/she will collect participants' baseline (T0) demographic data and study variables during a face-to-face interview. Block randomisation with a block size of 8, 10 or 12 will be used to ensure even distribution of participants between the two study groups. The block size and the respective allocation sequence to the intervention group receiving a modelling-based narrative intervention (by RA1) and control group receiving a didactic education (by RA2), will be determined by a computer-generated sequence. Participants chronologically recruited to the study will be allocated to the study groups by RA1 according to the computer generated sequence. Another independent RA (RA3), who is blinded to the study group allocation, will collect the post-intervention data. To detect short-term and long-term intervention effects, the outcome variables will be measured repeatedly at 3 (T1), 12 (T2) and 24 (T3) months following baseline data collection for both study groups. This extended period of outcome evaluation permits the study to detect the intervention effects on participants' actual care-seeking behaviours. Previous studies indicated that approximately 16% of these patients experienced AMI symptoms within two years. In the data collection telephone calls, the RA3 will enquire about whether the participants have been admitted to an emergency department with the experience of AMI symptoms. The study participants and their next of kin are strongly advised to contact the RA if they have been admitted due to a possible AMI attack.

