### Study participants

Patients will be eligible to join the study if they are (1)  $\geq 18$  years of age, (2) living in the community, (3) with a confirmed diagnosis of a prior AMI attack, (4) consent to participate and (5) those who can read Chinese. Individuals who do not understand Cantonese, with impaired communication ability, psychiatric problems or impaired cognitive functioning (i.e. Abbreviated Mental Test  $\leq 6$ ) which may hinder participation in the interventional activities will be excluded. For the RCT study, the sample size is determined on the basis of a large-scale RCT examining the effect of a brief nursing educational intervention on care-seeking knowledge, attitudes and beliefs related to AMI in people with CAD. The effect sizes for knowledge, attitudes and beliefs were 0.39, 0.24 and 0.23 at 3 months after the intervention. In consideration of both clinical relevance and previous study findings, the sample size of this study is determined to give the study adequate power to detect at least a small to medium effect size on the primary outcomes. Using PASS 13 (NCSS, Kaysville, USA), it is estimated that a sample size of 252 subjects per study arm would give the study 80% power at 5%

level of significance to detect an effect size as small as 0.23 on our primary outcomes between the control and intervention arms at the post intervention time points. Further allowing for a potential dropout rate of up to 20%, a total of 315 subjects per arm will be recruited. For the qualitative phase, a criterion sampling of 30 participants who have received the modelling-based narrative intervention will be invited to join on the basis of their prehospital delay time, which will be categorised into three groups:  $\leq 2$  hours,  $> 2$  and  $\leq 6$  hours, and  $> 6$  hours. The criterion is set according to the international AMI management guidelines, where such cut-offs are used to categorise patients into early, intermediate and late responders. A total of 30 participants will be recruited, with 10 participants for each category. Maximum variations in the sociodemographic and clinical profile of the participants will also be adopted in the sampling procedure to illustrate a wider range of data.

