#### Data analysis

For the RCT study, data analysis will be performed on an intention-to-treat basis. Baseline characteristics between the two study arms will be compared by t-test, chi-square or Fisher's exact test

where appropriate. A generalized estimating equation (GEE) model will be used to compare the differential changes on the outcomes across the time points T0, T1, T2 and T3 between the two study arms with adjustment for potential confounding variables. Baseline characteristics with p values < 0.25 for between-group difference will be considered as potential confounding variables. GEE model can account for intra-correlated repeated measures data and accommodate missing data caused by incomplete visits or dropout, provided that the data are missed at random, and thus are particularly suitable for intention-to-treat analysis without the need of imputation for missing data. All statistical analyses will be performed using IBM SPSS 23.0. All statistical tests will be two-sided and a p-value < 0.05 will be considered statistically significant. For the qualitative study, the audio-taped data will be transcribed verbatim. The investigation team will ensure accuracy of the transcription by cross-checking. Content analysis will be adopted to code the qualitative data on participants' perceptions and acceptability of the modelling-based narrative intervention. The analysis will also seek to understand why and how the study intervention influences patients' care-seeking behaviours. The codes units will be organised into categories and subcategories, which will be analysed for emerging themes. The trustworthiness of the qualitative analysis will be enhanced by audio-taping of the interviews, conducting an audit trail, involving two team members to code the qualitative data independently.

**Figure 1.** Study implementation protocol

[figure not shown]

**Figure 2.** Graphical presentation of the modelling-based narrative intervention protocol

[figure not shown]

**Table 1.** The storyline of the narrative video-based virtual heart attack experiencing session

**Background information of the model patient:** **[name]**, 58 year-old man, bus driver, non-smoker, with hypertension and hyperlipidaemia. He sustained a musculoskeletal injury over his chest region a week ago

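### Both arms are treated in small groups, but the sample size makes no allowance for clustering and the analysis is justified only for repeated measures within a participant

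*Protocol*

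**What the plan says.** Randomisation is individual. Under Study design, the protocol states: "Participants chronologically recruited to the study will be allocated to the study groups by RA1 according to the computer generated sequence". Blocks are used for balance between the arms.

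Treatment is given in groups in both arms. Under Study interventions, the intervention has "three weekly 90-minute face-to-face sessions in a small group of 6-8 participants", followed by a booster session. The reason for the format is explicit: "The small group format is adopted because it is effective in providing peer support and facilitating peer learning". The same section describes group discussion, shared problem-solving and role-play. The control is a single didactic session, "delivered in a small group (6–8 participants/group) format by another RA (RA2").

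The sample size, under Study participants, rests on an effect size of 0.23, power, significance level and 20% dropout: "252 subjects per study arm would give the study 80% power at 5" per cent significance, raised to 315 per arm for dropout. No ICC, design effect or number of groups is given.

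Under Data analysis, the model is a GEE across baseline and three follow-up times, chosen because "GEE model can account for intra-correlated repeated measures data" and can accommodate missing visits. The delivery group does not appear as a cluster, a random effect or a recorded analysis variable.

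**The concern.** People who discuss, role-play and solve problems together over several sessions may end up with more similar beliefs and attitudes than people in different groups. Beliefs and attitudes are the primary outcomes. Delivery groups are nested within arm, so variation between groups enters the arm comparison directly. A GEE with the participant as cluster allows for correlation between one person's visits but not between members of one group.

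If that correlation is positive, p-values are too small, confidence intervals too narrow and planned power too high. The error favours declaring a benefit on the primary comparison. The point estimate is not biased by it.

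**Working it through.** **Inputs from the protocol.** Groups of 6–8 in both arms; 252 per arm analysed and 315 recruited; effect size 0.23; two-sided 5%; 80% power.

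**Assumption.** The ICC within a delivery group is not given. I use 0.01, 0.02, 0.05 and 0.10.

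**Step 1: the plan's own figure.** For two means, n per arm = 2 × [(1.96 + 0.842)/0.23]² = 297, not 252. With 252 per arm, power at 0.23 is Φ(0.23 × √126 − 1.96) = Φ(2.582 − 1.96) = 73%. The figure of 252 corresponds to an effect size of 0.25. The dropout step is right: 252/0.80 = 315. So the baseline for any loss from clustering is 73%, not 80%.

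**Step 2: formulas.** With groups of m = 7:

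- Design effect, both arms clustered: DE = 1 + (m − 1) × ICC.
- Design effect, intervention arm only: the average over the arms, (DE + 1)/2.
- True type I error of the nominal 5% test: 2 × [1 − Φ(1.96/√DE)].
- Power of a valid test: Φ(2.582/√DE − 1.96).

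**Step 3: results.**

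| ICC (assumed) | DE, both arms | Type I error | Power | DE, intervention arm only | Type I error | Power |
|---|---|---|---|---|---|---|
| 0 | 1.00 | 5.0% | 73% | 1.00 | 5.0% | 73% |
| 0.01 | 1.06 | 5.7% | 71% | 1.03 | 5.4% | 72% |
| 0.02 | 1.12 | 6.4% | 68% | 1.06 | 5.7% | 71% |
| 0.05 | 1.30 | 8.6% | 62% | 1.15 | 6.8% | 67% |
| 0.10 | 1.60 | 12.1% | 53% | 1.30 | 8.6% | 62% |

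**Step 4: sensitivity to group size.** With both arms clustered, groups of 6 to 8 give a type I error of 5.6–5.8%, 6.2–6.6%, 8.0–9.2% and 11.0–13.3% at the four ICCs. If 20% drop out evenly, a group of 7 leaves 7 × 0.8 = 5.6 analysed members. The design effects are then 1 + 4.6 × ICC = 1.05, 1.09, 1.23 and 1.46, slightly below the values for groups of 6.

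**Step 5: simulation.** With no true effect, 36 groups of 7 per arm (252), three visits averaged per participant and 2,000 runs, participant-level robust errors rejected in 5.6%, 7.2%, 11.1% and 14.8% of runs at single-visit ICCs of 0, 0.02, 0.05 and 0.10. Clustering on the group gave 5.1–5.9%. The rates exceed those in the table because averaging visits removes visit-to-visit noise but not the group effect. In the simulation, total variance is 1 at one visit and 0.6 + 0.4/3 = 0.733 for the mean of three, so an ICC of 0.05 becomes 0.05/0.733 = 0.068.

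**Step 6: number of clusters.** 315/8 to 315/6 gives about 39 to 53 groups per arm, enough for a group-level robust variance.

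**The case against.** The strongest reply is that the harm depends on a quantity the protocol does not give. A reader might infer that the standard errors are certainly too small. The documents do not establish that: it requires a positive ICC, and at 0.01 the effect is slight (5.7% instead of 5%). One research assistant is named as deliverer in each arm, and a standardised manual and fidelity checks apply. These limit differences between groups, though they do not remove peer influence.

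A reader might also apply one ICC to both arms. The text gives the peer-learning rationale only for the intervention. The control is a single slide-based session, with questions answered from structured content, so its ICC may well be lower. The columns for clustering in the intervention arm only show that case.

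A third tempting reading sets 68%, 62% or 53% power against the stated 80% and blames clustering for the whole gap. About 7 points of that gap exist with no clustering at all.

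Finally, the protocol does not name the GEE's cluster unit or variance estimator, and a statistical analysis plan may do so. That is fair for the analysis: the protocol does not expressly rule out clustering on group. It does not answer the rest. The sample size is fixed here with no allowance. The only correlation cited in support of the model is within a participant. Attendance is recorded, but nothing says that delivery-group membership will be kept for analysis, and a later plan cannot use a variable that was not captured.

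**Conclusion.** The point holds in conditional form. The protocol combines individual randomisation with group delivery in both arms, leaves clustering out of the sample size, and justifies its model only by repeated measures. If outcomes within delivery groups are positively correlated and the GEE is clustered on the participant, the primary inference is anti-conservative and the power overstated.

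The size is not known from the documents. Over the assumed ICC range it runs from almost negligible to more than a doubling of the nominal error rate, and it is smaller throughout if only the interactive arm is clustered. The part of the power loss due to clustering is measured from 73%: about 2 to 20 points with both arms clustered, and about 1 to 11 with the intervention arm only. The failure of 252 per arm to give 80% power at 0.23 is a separate matter.

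**What to change.** 1. **Record the group.** Assign each randomised participant to a delivery group when groups are formed, and store its identifier. The protocol describes allocation to arm only, so this step has to be written in. Participants who never attend stay in the group they were scheduled for; those never scheduled are treated as clusters of one.
2. **Use it in the analysis.** Make the delivery group the cluster for the GEE robust variance. Alternatively, fit a mixed model with a random group effect, allowed to differ by arm, plus within-person correlation.
3. **Restate the power** for the planned 315 per arm (252 after 20% dropout) over a stated ICC range, starting from the correct figure without clustering.

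The cost is one data field, captured while groups are being formed, and a change to the model specification. Confidence intervals become somewhat wider and the stated power falls; enrolment does not change. That accepts the lower power. Even taking 252 per arm as the base, offsetting clustering in both arms would need 252 × DE: 278–288 per arm before dropout at an ICC of 0.02, and 378–429 at 0.10, for groups of 6 to 8.

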#### Fidelity monitoring of the study interventions

Multiple methods will be used to monitor the fidelity of the study interventions. First, the PI will randomly select five groups in each study arm for monitoring. The face-to-face sessions will be audio-taped after obtaining participants' consent. A performance checklist will be used for the purpose of fidelity monitoring. Two research fellows will review the tapes and complete the checklist after an orientation session with the PI. Secondly, a standardised manual will be developed to guide the intervention. Thirdly, the research assistants will keep reflective notes after each session and discuss the intervention with the investigation team on a regular monthly basis. The attendance of the participants will be recorded. All data will be used for data interpretation.

#### Outcome measures

The Acute Coronary Syndrome Response Index (ACSRI-C, Chinese version) will be used to measure the knowledge of AMI symptoms, care-seeking beliefs and attitudes upon symptoms occurrence. The knowledge subscale consists of 21 items to be responded dichotomously (yes/no). A four-point Likert scale is used to respond to the attitudes (5 items) and beliefs subscales (7 items). Higher scores indicate better knowledge, more appropriate care-seeking attitudes and beliefs. The ACSRI-C has good reliability (Cronbach's alpha = .81), convergent and construct validity.

The use of ambulance is defined as the primary means of selecting an ambulance as the transportation modality to hospitals. It will be retrieved from medical records and doubly confirmed with the participants.

The prehospital delay time is defined as the time interval between onset of acute symptoms and the documented time of arrival at a hospital's emergency department. The time of symptom onset will be elicited by patients' recall. To ensure its accuracy, a validated benchmarking technique in which the time of symptom onset is placed in the context of routine events that surround symptom onset will be used. The hospital arrival time will be retrieved from the patient's medical record.

